### 2.4 Interventions

1) The test group will receive oral JHG in the morning and evening for 3 months. JHG will consist of 30 g of *Astragalus mongholicus* Bunge [Fabaceae; Astragali radix], 10 g of *Panax ginseng* C. A. Mey. [Araliaceae; Ginseng radix et Rhizoma], 30 g of *Poria cocos* (Schw.) Wolf [Polyporaceae; Poria fungus nucleus], 10 g *Epimedium brevicornu* Maxim. [Berberidaceae; Epimedii folium], and 6 g of *Arisaema erubescens* (Wall.) Schott [Araceae; Arisaematis rhizoma preparatum]. JHG will be prepared as follows: five ingredients will be decocted twice with 3-fold distilled water according to the above ratio at each course for 1 h. The decocting solution will then be combined. The supernatant obtained by high-speed centrifugation will be concentrated at 50°C to a relative density of 1.08–1.10 g/ml. Subsequently, the same amount of 95% ethanol will be added, stirred and left to stand for 24 h. The supernatant will be filtered and the ethanol recovered, then further concentrated at 50°C to a relative density of 1.30–1.32 g/ml. Dextrin will be added and the solution will be granulated in a fluidised bed granulator. The obtained particles will be dried under vacuum at 50 °C for 1 h, packaged, and stored at 4°C.2) The control group will receive oral placebo (mostly dextrin containing 10% of the dosage of JHG determined by appearance, color, clarity, odor and taste through several experiments) in the morning and evening for 3 months. The preparation process of the placebo will be the same as that of JHG.

JHG and placebo will be provided by Beijing Temages Pharmaceutical Co., LTD. (Beijing, China). The characteristics, particle size, moisture content, volume difference, and solubility of the JHG and placebo will be examined according to the granule section of the Pharmacopoeia of the People’s Republic of China (2020 edition).

### 2.5 Combined medications and treatments

All participants will be required to adhere to the following guidelines for combination medication and treatment during the trial period:

#### 2.5.1 Combined medications

1) Participants will be advised not to take herbal medicines containing *Epimedium* or *Arisaema* species.2) Other drugs that must be continued when patients with other diseases are enrolled should be recorded in the medical record report form along with the participant’s other diseases and medication history.3) Researchers will ask the participants to bring all the medications they were using at the hospital during the interview to check for their combinatory effects. Drugs or other therapies that must be continued must be documented in medical records, including dosage, frequency, and time of use for analysis and reporting.

#### 2.5.2 Combined treatments

Participants will be allowed to receive the necessary treatments for other illnesses or symptoms (unrelated to this indication); however, the treatment should be accurately and carefully documented in the study records.

### 2.6 Outcomes

#### 2.6.1 Primary outcomes

1) Disease-free survival will be defined as the time from the date of randomisation to the date of recurrence, metastasis, or death from any cause.2) Recurrence and metastasis rates at 1, 2, and 3 years.

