## Abstract

**Background:** The high incidence and mortality rates of colorectal cancer (CRC) are a severe challenge in China. In patients with stage III and high-risk stage II CRC after radical resection and postoperative adjuvant chemoradiotherapy, 40–60% experience recurrence and metastasis. Several years of clinical practice have shown that traditional Chinese medicine, including Jianpi Huatan granule (JHG), effectively prevents stage III and high-risk stage II CRC recurrence and metastasis after radical resection and postoperative standard adjuvant chemotherapy. However, high-level systematic plans and evidence-based medicine are lacking in this regard. Therefore, this randomised control trial aimes to determine the efficacy of JHG in reducing stage III and high-risk stage II CRC metastasis and recurrence after radical resection and postoperative standard adjuvant chemotherapy.

**Methods:** This is a multicentre, randomised, double-blind, placebo-controlled clinical trial. Three hundred and fifty patients with stage III or high-risk stage II CRC who completed adjuvant chemotherapy after radical resection will be recruited from eight medical centres in China and randomly assigned to test (n = 175) and control (n = 175) groups at a ratio of 1:1. The test group will receive oral JHG for 3 months, whereas the control group will receive oral placebo for 3 months. The primary outcomes will be the disease-free survival and 1-, 2-, and 3-years metastasis and recurrence rates, whereas the secondary outcomes will be quality of life and circulating tumour cells. The patients will be followed-up monthly during treatment and every 3–6 months thereafter until recurrence, metastasis, death, or the end of the study.

**Trial registration:** This trial was registered at ClinicalTrials.gov (NCT03716063).

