### 2.9 Sample size calculation

The sample size was estimated using the PASS software (version 11; NCSS, LLC, Kaysville, UT, United States) and a log-rank test. The final sample size depends on several factors, including the occurrence of primary endpoint events.

The main endpoints of this study will be the postoperative recurrence and metastasis of stage II and III CRC. In previous studies (Xu et al., 2017; Yang et al., 2008), the 3-years recurrence and metastasis rates in the treatment and control groups were 18 and 31%, respectively. In this study, we used a 1:1 distribution design and an 80% test efficiency. The false-positive error rate will be controlled within 5% (both sides), and the annual loss rate in the follow-up period will be controlled within 5%. Based on the above hypothesis, 342 patients (171 and 171 in the experimental and control groups, respectively) were enrolled after a 1-year recruitment period and 3-years follow-up period. The number of expected endpoint events is 88 (33 in the experimental group and 55 in the control group). A minimum of 342 patients is required. This study will enrol 350 patients (175 in each group).

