#### 2.10.1 Selection of analytical data sets

1) *Full analysis set:* The ideal set of participants will match the principle of intentionality analysis (mainly including all randomised participants) as closely as possible. The dataset was obtained by eliminating all randomised participants using the smallest and most reasonable method.2) *Compliance scheme set:* In compliance with the experimental treatment scheme, the main variables can be measured, baseline variables will not be missing, and no major violations of the experimental scheme will be observed.3) *Safety set:* All participants will receive at least one treatment after randomisation.4) The full analysis set and compliance scheme set will be subjected to curative effect analysis, whereas the full analysis set will be used to analyse demographic and other baseline characteristics and therapeutic indicators.

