#### 2.10.3 Statistical analysis method

1) Descriptive statistical analysis: Qualitative indicators will be described using frequency tables, percentages, or constituent ratios, while quantitative indicators will be described using mean and standard deviation or median, lower quartile (Q1), upper quartile (Q3), minimum, and maximum.2) Two groups of comparative analyses will be conducted. For qualitative data, the chi-square test, Fisher’s exact probability method, Wilcoxon rank-sum test, Cochran–Mantel–Haenszel-2 test, and weighted least-squares covariance test will be used. Quantitative data will be tested for normal distribution using a *t*-test (homogeneity test of variance between groups with a test level of 0.05, and the Satterthwaite method for correction of the *t*-test results when the variance is uneven). The Wilcoxon rank-sum test will be used in cases of non-conformity to the normal distribution, Kaplan–Meier survival analyses will be performed, and the Cox proportional risk model will be used for survival data. The hypothesis test uses a bilateral test and generates test statistics and corresponding P values. The test level will be set at 0.05, and statistical significance will be set at P < 0.05.

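### Four unranked primary outcomes and a flat 0.05 test level do not secure the promised 5% false-positive rate; if success on any one counts, it is about 11–13%

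*Protocol article*

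**What the plan says.** The Abstract lists the outcomes together: "The primary outcomes will be the disease-free survival and 1-, 2-, and 3-years metastasis and recurrence rates". Section 2.6.1 repeats this as two numbered items. The first is a time-to-event outcome: "Disease-free survival will be defined as the time from the date of randomisation to the date of recurrence, metastasis, or death from any cause". The second is "Recurrence and metastasis rates at 1, 2, and 3 years". Neither place ranks the items, splits the error rate between them, or says whether all must succeed.

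Section 2.9 sizes the trial with one log-rank test. It states "we used a 1:1 distribution design and an 80% test efficiency" and "The false-positive error rate will be controlled within 5% (both sides"). Its inputs are 3-year recurrence/metastasis rates of 18% and 31%, a 5% annual loss, one year of recruitment and three of follow-up. Its results are 342 patients (350 planned) and 88 events (33 + 55).

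Section 2.10.3 sets one level for hypothesis tests: "The hypothesis test uses a bilateral test and generates test statistics and corresponding P values", and then "The test level will be set at 0.05, and statistical significance will be set at P < 0.05". It assigns Kaplan–Meier and Cox methods to survival data, and chi-square and related tests to qualitative data. It does not say which of these applies to the landmark rates.

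**The concern.** Section 2.9's 5% promise refers to one comparison, while the Abstract and section 2.6.1 name four outcomes of equal standing. As written, a trial with a negative log-rank result but P < 0.05 for, say, the 1-year rate could be reported as positive on a primary outcome, and nothing in the article would contradict that report.

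The article does not make it obvious that DFS is the real primary. Section 2.9 describes the main endpoints as postoperative recurrence and metastasis, takes its effect size from 3-year rates and does not mention DFS. The Introduction and Discussion also state the aim as lower metastasis and recurrence rates. The landmark rates could therefore carry the headline claim.

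This is more than a detail left to a statistical analysis plan. The set of primary outcomes is fixed in this document, and a later plan that picked one would have to override the Abstract and section 2.6.1.

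**Working it through.** **1. Reproduce the design for one test.** Inputs are from section 2.9; exponential event and loss times are assumed.

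- Hazards per year: −ln(0.82)/3 = 0.0662 (test) and −ln(0.69)/3 = 0.1237 (control). Hazard ratio = 0.535.
- Events needed, two-sided 0.05 and 80% power: Freedman 7.849 × [(1 + 0.535)/(1 − 0.535)]², giving 86; Schoenfeld 4 × 7.849/(ln 0.535)², giving 81.
- Loss hazard g = −ln(0.95) = 0.0513. With uniform one-year accrual and four years in total, and h = λ + g, the event probability is (λ/h) × [1 − (e^(−3h) − e^(−4h))/h] = 0.190 (test) and 0.323 (control).
- Expected events with 171 per arm: 32.4 + 55.3 = 87.7, against 33 + 55 = 88 stated. Freedman's 86 events need about 335 patients, within 3% of 342.

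The sizing is sound for a single log-rank test at 0.05.

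**2. Bounds for four tests at 0.05.** If independent, 1 − 0.95⁴ = 18.5%. The Bonferroni bound is 4 × 0.05 = 20%. Both are too high here because the four tests use largely the same events.

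**3. Large-sample calculation with correlation.** For a null 3-year rate p, let λ = −ln(1 − p)/3, F(t) = 1 − e^(−λt) and v(t) = F(t)/(1 − F(t)). Then:

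- corr(landmark s, landmark t) = √[v(s)/v(t)] for s < t;
- corr(log-rank, landmark t) ≈ λt/√[F(T)·v(t)], with T = 3.5 years as the average follow-up.

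At p = 0.31, the log-rank test correlates 0.575, 0.788 and 0.934 with the 1-, 2- and 3-year rates, and the 1-year rate correlates 0.541 with the 3-year rate. The probability that at least one of the four |z| values exceeds 1.96 is 12.1% at p = 0.18, 0.245 and 0.31, and 12.2% at p = 0.45.

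**4. Null simulation.** 175 per arm, equal hazards, accrual and loss as in section 2.9, 8,000 trials per scenario. Landmarks were tested either by Kaplan–Meier difference or by comparing crude proportions. Deaths were set at 0 or 1% a year; the death rate is an assumption.

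| Null 3-year rate | Any of four, Kaplan–Meier landmarks (no deaths / 1% a year) | Any of four, crude proportions (no deaths / 1% a year) |
|---|---|---|
| 18% | 11.6% / 12.9% | 11.4% / 12.7% |
| 24.5% | 12.4% / 12.4% | 12.1% / 11.8% |
| 31% | 12.1% / 12.4% | 11.6% / 12.4% |
| 50% | 12.9% / 13.0% | 11.8% / 12.6% |

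The log-rank test alone rejected in 4.8–5.5% of trials. With no loss and a fixed three years, the any-of-four figure was 11.2%. A separate run of 20,000 trials at a 31% rate gave 4.8% for log-rank alone and 11.9% for any of the four (Kaplan–Meier landmarks). So 11.9 − 4.8 = 7.1% of null trials showed a significant landmark beside a negative log-rank test.

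**5. Where the excess arises.** With a correlation of 0.93, DFS plus the 3-year rate alone gives about 6.7%. Most of the inflation therefore comes from the 1- and 2-year comparisons.

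**6. Cost of keeping four primaries.** At 0.05/4 = 0.0125, Freedman needs 122 events and about 476 patients, Schoenfeld 114 events and about 445. With 88 events, power would fall to about 64–67%.

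**The case against.** The tempting stronger reading is that each of the four outcomes will be tested at 0.05, so that the trial's error rate simply is 12%. The document does not support that. Section 2.10.3 sets a level for tests without assigning tests to outcomes, and no section says that one success suffices. If all four had to succeed there would be no inflation, although the power, computed for one test, would then be overstated.

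A benign reading is also available. Section 2.9 handles recurrence/metastasis as time-to-event data, so the landmark rates may be meant only as points read from one curve. A statistical analysis plan might also set a hierarchy. These arguments make the 12% conditional. They do not remove the mismatch between four equal primaries and a 5% promise built on one test, because the current text permits either reading.

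A reader might add that section 2.10.1 runs efficacy on two analysis sets ("The full analysis set and compliance scheme set will be subjected to curative effect analysis"). Using two sets is routine, the same item leans towards the full analysis set for therapeutic indicators, and no extra error has been quantified. Nor does the article say that landmark rates will be crude proportions, so any bias from patients lost to follow-up is a separate, conditional matter. Neither supports this point.

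One objection to the remedy stands: section 2.9 derived its 88 events from recurrence/metastasis rates, whereas DFS also counts deaths from any cause.

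**Conclusion.** The point holds in conditional form. The article fixes four unranked primary outcomes and a flat 0.05 level beside a promised 5% error rate that its sizing supports for one log-rank test only. If the landmark rates are tested and any one success counts, which the document neither states nor rules out, the familywise error is about 11–13%. That range assumes exponential event times, null 3-year rates of 18–50% and, in some scenarios, deaths at 1% a year; it barely moves across these. DFS by log-rank alone keeps about 5%.

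The matter deserves correction before unblinding because it decides what may be called a positive primary result.

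**What to change.** - **Sections 2.6.1 and Abstract:** name DFS as the single primary outcome. Move the 1-, 2- and 3-year rates to secondary outcomes, estimated from the Kaplan–Meier or cumulative-incidence curve with 95% confidence intervals.
- **Section 2.10.3:** state that the primary comparison is the two-sided log-rank test at 0.05 in the full analysis set, with the Cox hazard ratio and its 95% confidence interval as the effect estimate.
- **Section 2.9:** state that the 88 events came from recurrence/metastasis rates, and that DFS, which adds deaths, should yield at least about that many. Deaths unaffected by treatment also dilute the effect, and this should be acknowledged. As an illustration only, 1% a year in both arms gives a hazard ratio of (0.0662 + 0.01)/(0.1237 + 0.01) = 0.570. By the step 1 event formula, 342 patients then give about 96 events, and power is about 76% (Freedman) to 79% (Schoenfeld).

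The cost is wording. The planned 350 patients and the data collection stay as they are. The sponsor can no longer claim a landmark rate as a primary success.

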#### 2.6.2 Secondary outcomes

1) Quality of life score will be measured as follows:a) TCM symptom grade (Appendix 1) with the evaluation standards listed in Table 1.b) Functional Assessment of Cancer Therapy-Colorectal (FACT-C) (Version 4) scale (Appendix 2)*.* The FACT-C scale is divided into five grades: not at all (0), slightly (1), somewhat (2), quite a bit (3), and very much (4). Positive items (i.e. the higher the grade, the better the quality of life) will be directly scored from 0 to 4, whereas negative items will be reverse-scored. Items 1–7, 15, 17–20, 28, 29, 32, 35, and 36 are negative items. The scoring formula is as follows: forward item score = (0 + answer option number); reverse item score = (4 − answer option number). If there will be any unanswered questions, the score will be calculated by adding the scores of the answered questions to the total number of questions answered. The scores of all the fields will be summed to obtain the total score.c) Edmonton Symptom Assessment Scale (ESAS) (Appendix 3)*.* The scale uses a digital scoring method, with each symptom scored between 0 (asymptomatic) and 10 (most serious). Patients will choose a number to express their feelings, with a higher number indicating more serious symptoms. The points will be divided into three degrees: mild, 1–3; moderate, 4–6; and severe, 7–10.2) Circulating tumour cells (CTCs) will be counted in the peripheral blood after randomisation and 3 months later.

**TABLE 1 T1:** Treatment efficacy according to TCM Symptom Scale Score.

Effect level	Definition
Significantly effective	TCM Symptom Scale score decreased by >50% after versus before treatment
Effective	TCM Symptom Scale score decreased by 30–50% after versus before treatment
Ineffective	TCM Symptom Scale score decreased by <30% after versus before treatment

TCM, traditional Chinese medicine.

#### 2.6.3 Safety evaluation

1) All adverse events, including symptoms and signs.2) General physical examination (height, weight, body temperature, blood pressure, heart rate, etc.) and essential physical examination (endocrine system and other special clinical parameters) data.3) Laboratory examinations including routine blood tests, liver and kidney function tests, stool and occult blood tests, urine tests, and 12-lead electrocardiography.

### 2.7 Follow-up

#### 2.7.1 Follow-up time

The patients will be followed-up monthly during treatment and every 3–6 months thereafter until recurrence, metastasis, death, or the end of the study.

#### 2.7.2 Follow-up measurements/observations

##### 2.7.2.1 During treatment

1) Baseline physical examination parameters will include height, weight, blood pressure, and heart rate.2) The safety indicators for each follow-up will include blood, urine, routine, stool, liver, and kidney function, and electrocardiography.3) Imaging examination data of patients will be collected and recorded during treatment.4) The participants in the group will be tested for CTCs after enrolment and again after treatment completion.5) Symptom-based assessment will include the quality of life scale.

##### 2.7.2.2 After treatment

Follow-up observations will focus on metastasis and recurrence.

#### 2.7.3 Follow-up method

Patients will mainly be followed-up at outpatient clinics during treatment and by telephone until the observation deadline or endpoint events occur. The observation deadline will be the last day of contact.

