### 2.3 Participants recruitment

#### 2.3.1 Inclusion criteria

1) Clear pathological diagnosis of CRC that conforms to Western medicine diagnostic criteria;2) Radical resection of CRC was performed, and at least 3 months of standard adjuvant chemotherapy administered before starting the trial, including preoperative neoadjuvant therapy for rectal cancer;3) TNM stage III or high-risk stage II;4) Age 18–80 years for both sexes;5) No recurrence or metastasis by imaging or doctor’s clinical judgment; and6) Provision of written informed consent.

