### 2.8 Data management and monitoring

All data will be obtained from the medical records completed by the researcher. Data will be collected using an electronic case report form. The data manager is responsible for managing data and establishing a dedicated database for the project. Data entry will be performed by trained personnel, who will subsequently ensure data quality and accuracy. To ensure data accuracy, two data administrators will independently perform double entries and proofreading. Table 2 presents the details of the data-collection process.

**TABLE 2 T2:** Study data collection process.

Study period											
Research stage	Enrolment	Intervention			Follow-up						
Visit number	1st	2nd	3rd	4th	5th	6th	7th	8th	9th	10th	11th
**Time point**	**Day 0**	**Day 30**	**Day 60**	**Day 90**	**Month 6**	**Month 9**	**Month 12**	**Month 18**	**Month 24**	**Month 30**	**Month 36**
Baseline basic information collected											
Eligibility screen	✔										
Informed consent	✔										
Demographic information	✔										
Medical and treatment history	✔										
Combined disease	✔	✔	✔	✔	✔	✔	✔	✔	✔	✔	✔
Combined medication	✔	✔	✔	✔	✔	✔	✔	✔	✔	✔	✔
Observation indices											
Recurrence and metastasis	✔	✔	✔	✔	✔	✔	✔	✔	✔	✔	✔
CTCs	✔			✔							
Vital signs	✔	✔	✔	✔							
Adverse reactions	✔	✔	✔	✔							
TCM Symptom Scale	✔	✔	✔	✔							
FACT-C	✔	✔	✔	✔							
ESAS	✔	✔	✔	✔							
Tumour markers	✔	✔	✔	✔							
Imaging examination	✔	✔	✔	✔	✔	✔	✔	✔	✔	✔	✔
Safety observations											
Routine blood tests	✔	✔	✔	✔							
Blood biochemistry tests	✔	✔	✔	✔							
Routine urine and stool test	✔	✔	✔	✔							
ECG	✔	✔	✔	✔							
Adverse events	✔	✔	✔	✔							

CTCs, circulating tumour cells; ECG, electrocardiography; ESAS, edmonton symptom assessment scale; FACT-C, functional assessment of cancer therapy-colorectal; TCM, traditional Chinese medicine.

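### Sections 2.7.2.1 and 2.7.3 do not fit Table 2 on how recurrence is ascertained after day 90, and observation is said to end at last contact, not last disease assessment

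*Protocol article*

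**What the plan says.** Section 2.6.1 makes DFS, and the recurrence and metastasis rates at 1, 2 and 3 years, the primary outcomes. It does not say how a recurrence is established. The passages that bear on this are:

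- **Section 2.7.2.1**, in its list for the treatment period (3 months): "Imaging examination data of patients will be collected and recorded during treatment". Section 2.7.2.2, for the time after treatment, names metastasis and recurrence as the focus and gives no method.
- **Section 2.7.3**: "Patients will mainly be followed-up at outpatient clinics during treatment and by telephone until the observation deadline or endpoint events occur". It then adds: "The observation deadline will be the last day of contact".
- **Section 2.8, Table 2**: the row "Imaging examination" is ticked at all 11 visits from Day 0 to Month 36. Seven of these (Months 6, 9, 12, 18, 24, 30 and 36) come after day 90. Recurrence and metastasis is a separate row with the same ticks, and nothing links the two rows.
- **Section 2.3.1**, criterion 5: "No recurrence or metastasis by imaging or doctor", with the doctor's clinical judgement as the second source. Table 2 also has imaging at Day 0.

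**The concern.** A site that reads sections 2.7.2 and 2.7.3 would telephone patients after day 90 and record what it learns. A site that reads Table 2 would obtain a scan at each of the seven later visits. A call cannot deliver a scan, and the article does not say that the call is used to retrieve one.

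The last-contact sentence adds to this. If it serves as the censoring rule, a patient who answers the telephone but has not been scanned is carried as disease-free to the day of the call. A recurrence present at that time is either never recorded or recorded later than it could have been. At stake are the absolute recurrence rates, which are themselves a primary outcome, and the number of DFS events on which the power rests. A scan that was never obtained cannot be recovered at the analysis stage.

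**Working it through.** **Inputs (section 2.9).** The plan assumes that "the 3-years recurrence and metastasis rates in the treatment and control groups were 18 and 31%, respectively" and uses "an 80% test efficiency", a two-sided 5% level, 1:1 allocation, 5% annual loss, 1 year of recruitment and 3 years of follow-up. It states 342 patients (171 per arm) and 88 events (33 + 55).

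**Step 1: reproduce the plan's figure.** With exponential survival the yearly hazards are −ln(0.82)/3 = 0.0661 and −ln(0.69)/3 = 0.1237, so HR = ln(0.82)/ln(0.69) = 0.535. The loss hazard is η = −ln(0.95) = 0.0513. The expected proportion with an event is λ/(λ+η) × [1 − mean of exp(−(λ+η)t)], with t uniform between 3 and 4 years. With 171 per arm this gives 32.4 + 55.3 = 87.7 events, against 88 stated. Required events are 86 (Freedman) or 81 (Schoenfeld), and Freedman's formula gives N = 335, within 3% of 342. The stated sample size is not in dispute.

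**Step 2: how many events fall after day 90?** Events in the first 0.25 year, ignoring loss:

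- test arm: 171 × [1 − exp(−0.0661 × 0.25)] = 2.8
- control arm: 171 × [1 − exp(−0.1237 × 0.25)] = 5.2

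The total is 8.0. Of 88 events about 80 remain, or 80/88 = 91%, in the period where the text and the table differ.

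**Step 3: what would missed recurrences cost?** The documents give no detection rate, so it is an assumption here. Let the same share s be detected in both arms. Then the recorded 3-year rates are 0.18s and 0.31s, events D = 88s, and HR = ln(1 − 0.18s)/ln(1 − 0.31s). Power is Φ(√D × |ln HR|/2 − 1.96) by Schoenfeld and Φ(√D × (1 − HR)/(1 + HR) − 1.96) by Freedman. For s = 0.90, D = 79.2 and HR = 0.540, giving Φ(0.78) = 78.2% and Φ(0.70) = 75.7%.

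| Detected (assumed) | Recorded 3-year rates, test / control | HR | Events | Power, Schoenfeld / Freedman |
|---|---|---|---|---|
| 100% | 18.0% / 31.0% | 0.535 | 88.0 | 83.5% / 81.1% |
| 95% | 17.1% / 29.45% | 0.538 | 83.6 | 81.0% / 78.5% |
| 90% | 16.2% / 27.9% | 0.540 | 79.2 | 78.2% / 75.7% |
| 80% | 14.4% / 24.8% | 0.546 | 70.4 | 72.0% / 69.4% |
| 70% | 12.6% / 21.7% | 0.551 | 61.6 | 64.9% / 62.4% |

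A log-rank simulation with the planned 350 patients, in which only recurrences after day 90 can be missed, agrees. Events fall from 90 to 82 or 73, and power from 83% to 78% or 73%, when 10% or 20% are missed.

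**Step 4: read the pattern.** The HR hardly moves (0.535 to 0.551 over the whole range). The loss is in events, power and the absolute rates. The expected 3-year difference shrinks from 13.0 points to 11.7 at 90% detection and 10.4 at 80%.

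**The case against.** A reader might infer that the three places flatly contradict each other, so that recurrence after day 90 rests on patient report alone. The text does not go that far. Section 2.7.2.1 does not say that imaging is confined to treatment. Section 2.7.3 says *mainly*, which leaves room for later clinic visits. Section 2.8 opens by saying that data come from medical records completed by the researcher. Table 2 leaves no gap longer than 6 months between scans. A consistent reading exists: patients are scanned on the Table 2 schedule and the telephone serves to keep contact and obtain results. This objection stands as to wording. It does not remove the need to say so, because the article nowhere does.

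It is also fair that sections 2.6.1 and 2.10.3 state no DFS censoring date, and that detailed censoring rules commonly sit in the analysis plan. Taking the last day of contact as the DFS censoring date is therefore an inference. But it is the only end-of-observation rule stated, and it is an unsuitable one for an endpoint that needs an examination to be seen.

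The detection rates in the working have no source in the documents. Treating a missed recurrence as never recorded is also pessimistic: many would surface at a later scan, through symptoms, or as a death, which is itself a DFS event. For those the effect is late dating.

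Finally, a reader might take criterion 5 to admit patients whose disease status was never imaged. Its negated wording can equally mean that neither source shows disease, and Table 2 places imaging at Day 0 beside the eligibility screen. The documents support a request for clarification there, and no figure for unrecognised disease at entry.

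**Conclusion.** The point holds in a limited form. The narrative and Table 2 do not fit together on how recurrence is ascertained in the period that carries about 91% of the expected events, and the stated end of observation is tied to contact, not to disease assessment. If the narrative is followed, DFS and the 1-, 2- and 3-year rates look too favourable in both arms, with some loss of events and power.

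The size cannot be fixed from the documents. Under an assumed 90% detection, equal in both arms, it is about 79 events and 76–78% power. If Table 2 imaging is done and its results reach the trial, the effect shrinks towards nothing.

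A reader might go further and infer a biased treatment comparison. That is not supported: equal under-detection leaves the HR almost unchanged, and double-blinding makes unequal detection less likely.

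**What to change.** 1. Reconcile sections 2.7.2.1, 2.7.2.2 and 2.7.3 with the imaging already scheduled in Table 2, so that all state one means of ascertaining recurrence at each visit after day 90. State that telephone contact serves to prompt and collect scan reports and to establish vital status.
2. Date a recurrence or metastasis by the examination that confirms it.
3. Censor DFS for patients without an event at the last disease assessment. Keep the last day of contact for vital status only.
4. Clarify in section 2.3.1 that criterion 5 is read together with the Day 0 imaging in Table 2.

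The cost is mostly wording, since no examination is added to Table 2. The downsides are slightly shorter censoring times and the work of collecting scan reports.
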